### Interim monitoring

An independent DSMB comprising three members with expertise in statistics, epidemiology and infectious diseases will be responsible for the interim monitoring process. The statistician at the Data-Coordinating Center will be the only person with access to the full database and he will provide the required information, both overall for the interim quality assurance and specific by treatment group (efficacy and safety) exclusively for the DSMB. The first interim monitoring will be conducted when the study participants complete six months of evaluation. The second interim analysis will be conducted when all the patients complete nine months of evaluation. Stopping guidelines for efficacy monitoring will be determined for the primary and secondary outcomes according to the modified O'Brien-Fleming procedure. With this procedure, the values for statistical significance are 0.0006 and 0.0151 in the first (α_1_) and second (α_2_) interim analyses, respectively, for a final significance (α) of 0.0471. Stopping guidelines for safety are left at discretion of the DSMB, with an expected rate of adverse events (hepatic or muscle enzymes elevations) less than 1%. Stopping guidelines regarding futility are not considered and this was agreed in a meeting with the DSMB.

### Analysis plan

The overall efficacy will be established with an intention-to-treat principle, in which the patients will be analyzed in the treatment group to which they were assigned by randomization. The outcomes viral load and CD4 T cells count, as well as most of tertiary/exploratory outcomes, are longitudinal data with repeated measurements and they require special statistical methods to account for the correlation among observations. To analyze this kind of clustered data it is necessary to model both the regression of *Y *(the outcome measure) on *x *(the intervention) and the within-cluster dependence. In a marginal model, the regression of *Y *on *x *and the within-cluster dependence are modelled separately with the application of the statistical method called generalized estimating equations (GEE), which was designed to provide valid regression inferences with correlated data [24].

When the regression analysis for the time-averaged difference in response between groups is the primary interest, as for our research, the *β *coefficient can be estimated by solving the estimating equation

Where *μ*_*i*_(*β*) = *E*(*Y*_*i*_), the marginal expectations for *Y*_*i *_is a vector, which comprises the *m*_*i *_observations (number of measurements) from the *i*^*th *^cluster (each patient). The marginal expectation is the average response over the population of individuals with a common value of *x *(lovastatin or placebo). The covariance matrix, *Cov*(*Y*_*i*_), for *Yi *depends not only on *β *but on α, which characterizes the within-cluster dependence or correlation among observations. This additional problem can be overcome by iterating until convergence between solving  and updating , an estimate of α [24]. This estimate of α may be approximated by the observed correlations in the data and by the assumption of the same correlation among pairs of *m*_*i *_observations (i.e. an exchangeable correlation structure). Additionally, the use of a robust variance estimator (Huber-White) produces valid standard errors even if the correlations within group are not as hypothesized by the specified correlation structure [25]. The GEE approach is simply to choose parameter values  so that the expected *μ*_*i*_(*β*) is as close to the observed *Y*_*i *_as possible, weighting each cluster of data inversely to its variance matrix, *Cov*(*Y*_*i*_; *β*, *α*), which is a function of the within-cluster dependence. These models have been used in the analysis of some interventions to prevent HIV infection in African American adolescents [26], and to evaluate the effect of interventions on outcomes related not only with HIV infection but other sexually transmitted diseases.

The β coefficient obtained with this procedure for the X variable is the estimated time-averaged change in the outcome measure in the lovastatin group compared with placebo, and its p-value is given by the Wald statistic . We will use the *xt *of commands from the statistical package Stata (StataCorp, 2007: Release 10, College Station, Texas, USA) for the proposed analysis of cross-sectional time-series datasets. Specifically, the command *xtgee *will evaluate population-averaged panel-data models using GEE. Although the expectation is that randomization assists in balancing known and unknown prognostic factors in a randomized clinical trial, this assignment process is not a guarantee against the possibility that estimates of treatment effect be modified by covariate imbalance. Accordingly, the estimated time-averaged change in the outcome measure for lovastatin vs. placebo will be adjusted by the most important prognostic factors (baseline CD4+ T cell count, baseline viral load, and adherence to the treatment) considered as additional independent variables in the same GEE model.

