### Study outcomes

The efficacy of lovastatin to control HIV-1 replication allowing an improved immune reconstitution will be determined by primary and secondary outcomes. The primary outcome will be the viral load measured as RNA copies per mL of peripheral blood, and the secondary outcome will be the CD4 T-cell count measured as cells per μL of peripheral blood; both determined at enrolment, and 6 and 12 months after the intervention.

The tertiary or exploratory outcomes will be the following (determined at enrolment, and 6 and 12 months of interventions, unless indicated otherwise):

- Absolute number per μL of peripheral blood of CD8+ T lymphocytes and the CD4/CD8 ratio

- Basal expression of immunological activation markers (CD38 and HLA-DR) on CD4+ and CD8+ T lymphocytes

- Concentration of total serum cholesterol

- Concentration of cellular cholesterol

- Functional activity of LFA-1 and ICAM-1

- Activity of Rho GTPases

- Monthly frequency and type of: infections, non-infectious AIDS defining diseases, hospitalizations

- Mortality due to an HIV-1/AIDS related cause

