### Biostatistical considerations

Primary hypothesis: The use of lovastatin (40 mg/day during one year) compared with placebo in HIV-1-infected individuals who are naïve for HAART, should result in a reduction of 50% or higher in viral load and an increase of 20% or higher in CD4 T cell count.

Documentation of outcome and follow-up: Primary and secondary outcome measures will be documented by investigators and research assistants masked to the subject's intervention group assignment.

Sample size and power: Based on a pilot test performed on 40 patients treated at the infectious diseases service, Hospital Universitario San Vicente de Paul (Medellin, Colombia), the baseline values for the primary and secondary outcome measures are as follows:

Mean viral load = 55,000 copies/mL; SD = 80,000 copies/mL

Mean CD4+ T cell count = 500 cells/mL; SD = 180 cells/mL

These outcomes, determined 6 and 12 months after the intervention, are longitudinal data with correlated measurements, and they need special considerations for calculation of power and sample size. In addition to the usual requirements of type I error, type II error, variation measurement and meaningful difference to be detected in longitudinal studies, it is necessary to know the number of repeated observations and an estimate of the correlation among them. The meaningful difference may be expressed as a time-averaged difference in response between groups. Assuming a fixed correlation of 0.8 among the three different measures of viral load, and a time-average difference of 50% between groups (i.e., a decrease of 22,500 copies/mL from the baseline value), with an alpha error of 0.05 and a beta error of 0.2, the sample size required is 55 patients per group. This sample size has more than 90% power to detect an increase of at least 20% in the baseline CD4+ T cell count. There will be not corrections for losses to follow-up or non-adherence, as the study is intended as a pilot phase II trial.

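### The single covariate set in the Analysis plan does not list the own enrolment value of the continuous tertiary outcomes, although that value is collected

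*Protocol article*

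**What the plan says.** The Study outcomes section introduces its last group of outcomes with "The tertiary or exploratory outcomes will be the following (determined at enrolment, and 6 and 12 months of interventions, unless indicated otherwise"). Most items in that list are continuous laboratory measures: CD8 count and CD4/CD8 ratio, CD38 and HLA-DR expression, serum and cellular cholesterol, LFA-1/ICAM-1 function and Rho GTPase activity. Two items are of another kind: "Monthly frequency and type of: infections, non-infectious AIDS defining diseases, hospitalizations", and "Mortality due to an HIV-1/AIDS related cause".

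The Analysis plan says that viral load and CD4 count, "as well as most of tertiary/exploratory outcomes, are longitudinal data with repeated measurements", and it proposes GEE for such data. It describes one treatment coefficient, the time-averaged difference between lovastatin and placebo. Because randomization may leave covariates unbalanced, it adds that this estimate "will be adjusted by the most important prognostic factors (baseline CD4+ T cell count, baseline viral load, and adherence to the treatment"), these being "considered as additional independent variables in the same GEE model". No other covariate set is given, and nothing says that the set changes with the outcome.

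**The concern.** In a longitudinal model the outcome's own pre-treatment value is usually the best single predictor of its later values. The named set supplies it for the primary and secondary outcomes only. A model for cholesterol or for CD38 on CD8 cells, fitted as written, would adjust for baseline CD4 and viral load but not for baseline cholesterol or CD38.

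The section's own reason for adjusting is chance imbalance. For a tertiary outcome the most relevant imbalance is in that outcome's own enrolment value, and the list leaves it uncontrolled. The tertiary outcomes carry the mechanistic question of the trial, with 55 patients per arm, so avoidable width in their confidence intervals matters.

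**Working it through.** The article gives no precision or power figure for the tertiary outcomes, so there is none to reproduce. The arm size of 55 (Biostatistical considerations) is taken as given.

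**Inputs.** From the article: 55 per arm, measurements at enrolment and months 6 and 12, exchangeable correlation. Assumed: the correlation r for a tertiary outcome, shown over a range; a difference of 0.4 SD for the power illustration; two-sided alpha of 0.05; months 6 and 12 as the responses.

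**Formulas**, in SD units:

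- Variance factor without the own baseline: V0 = (1 + r)/2
- Variance factor with the own baseline: V1 = (1 + r)/2 − r²
- Variance of the treatment effect: 2V/55
- Detectable difference at 80% power: (1.96 + 0.8416) × √(2V/55)
- Power: Φ(0.4/√(2V/55) − 1.96)

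| r | V0 | V1 | Variance cut | Detectable difference, SD | Power at 0.4 SD |
|---|---|---|---|---|---|
| 0.3 | 0.65 | 0.56 | 14% | 0.43 to 0.40 | 74% to 80% |
| 0.5 | 0.75 | 0.50 | 33% | 0.46 to 0.38 | 68% to 84% |
| 0.8 | 0.90 | 0.26 | 71% | 0.51 to 0.27 | 60% to 98% |

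**Allowing for the covariates already listed.** Suppose baseline CD4 and viral load together explain 20% of the outcome variance at every visit. The remaining correlation is r′ = (r − 0.2)/0.8, and the further cut from the own baseline is r′²/[(1 + r′)/2].

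- r = 0.3: r′ = 0.125, cut = 0.0156/0.5625 = 2.8%
- r = 0.5: r′ = 0.375, cut = 0.1406/0.6875 = 20.5%
- r = 0.8: r′ = 0.75, cut = 0.5625/0.875 = 64.3%

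**Simulation check.** GEE fits with exchangeable correlation and robust standard errors, 55 per arm, true effect 0.4 SD, CD4 and viral load unrelated to the outcome, 300 runs per setting. The first two rows use months 6 and 12 as responses; the last two use enrolment, month 6 and month 12. Cells give power, and in the third row also the mean estimate.

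| Model | r = 0.3 | r = 0.5 | r = 0.8 |
|---|---|---|---|
| Own baseline not included | 0.78 | 0.72 | 0.55 |
| Own baseline as covariate | 0.81 | 0.86 | 0.98 |
| Three responses, treatment term only | 0.48 (estimate 0.27) | 0.46 (0.28) | 0.28 (0.25) |
| Three responses, treatment-by-post-baseline term | 0.51 | 0.71 | 0.96 |

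The first two rows agree with the formulas within simulation error. In the third row the enrolment visit carries no treatment effect, so the coefficient is expected at 2/3 × 0.4 = 0.27.

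**The case against.** The strongest objection is that the enrolment value may not be left out at all. Biostatistical considerations has "Assuming a fixed correlation of 0.8 among the three different measures of viral load", and Study outcomes measures viral load at enrolment, 6 and 12 months, so enrolment may be one of the responses. A reader might infer that the tertiary outcomes are analysed with no use of their baseline. The article does not establish that; it shows only that the own baseline is not listed as a covariate. This part of the objection stands. It does not rescue the plan, however. The Analysis plan describes a single treatment coefficient, and with enrolment among the responses that coefficient shrinks to about two thirds of the true effect. A treatment-by-post-baseline term would be on target, and at r = 0.8 it would recover most of the precision, but no such term is described.

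A second objection is that an article need not give covariate sets for exploratory assays, which a statistical analysis plan commonly holds. That limits the weight of the point. It does not remove it, because this article names a set and places it in the same model instead of deferring the choice.

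A third objection is that the size is not anchored in the article. This also stands. The only stated correlation is for viral load, whose own baseline is already in the list.

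**Conclusion.** The point holds as a minor one, limited to the continuous tertiary outcomes measured at enrolment. If months 6 and 12 are the responses, the gain in variance from adding the own baseline runs from about 3% (r = 0.3, with 20% already explained by the listed covariates) to 71% (r = 0.8, with nothing explained). Where a given assay falls in that range cannot be read from the article.

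Two stronger readings are not supported. One is that every outcome lacks its own baseline. Viral load and CD4 count have theirs, only most of the tertiary outcomes are brought under GEE, mortality and monthly events have no enrolment measurement to adjust for, and baseline CD4 partly serves the CD4/CD8 ratio. The other is that the tertiary results would be biased. Under randomization, leaving out a baseline covariate costs precision only. No efficacy conclusion on the primary or secondary outcome depends on this.

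**What to change.** Add one sentence to the Analysis plan: each continuous longitudinal tertiary outcome is modelled at months 6 and 12, with its own enrolment value as a covariate and not as a response. Baseline CD4 and baseline viral load can stay as optional further covariates. The sentence should name the outcomes it covers, so that mortality and the monthly clinical events are clearly outside it.

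The data are already collected, and the cost is about one degree of freedom per model. Whether adherence, which is observed after randomization, belongs in the same set is a separate question that this change does not settle.

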### Clinical follow-up

Before the enrolment and monthly during the study, all the patients will have a complete clinical evaluation performed by a physician who is blinded for the intervention assigned to each patient. Before the intervention (day 0) and 30, 180 and 360 days of study, blood samples will be collected to perform laboratory analysis (transaminases, CPK, serum lipid profile). The intervention will be stopped in presence of serious adverse events, a three-fold increase in serum transaminases or a five-fold increase in CPK. In order to preserve the blinding process, only the first value of serum lipid profile (day 0) will be known by the clinical investigators (eligibility criteria). Afterwards, for the samples at 180 and 360 days of following, a medical safety monitor in the DCC will receive the report directly from the laboratory.

The following clinical and pharmacotherapy parameters will be evaluated monthly for one year, during the medical control visits:

- Tolerance to medications and adverse events

- Adherence to therapy (lovastatin or placebo) and prevention of withdrawals

- Incidence of infections (opportunistic and non-opportunistic)

- Incidence of non-infectious diseases defining AIDS

- Hospitalizations due to diseases related to progressive HIV-1-infection

- Death due to diseases related to progressive HIV-1-infection

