### Interventions and safety of statins

After the first medical appointment and then monthly, each participant will receive the whole therapy for 1 month (60 tablets of lovastatin or placebo) from the pharmacist who also evaluates adherence to the intervention and gives usage recommendations. The statins are well tolerated by most persons; they have proven to be extremely safe in the vast majority of patients. Few significant side effects have been observed in clinical trials, and post-marketing reports of adverse events have been very limited when considered in comparison to a very large number of persons safely using them. The main risks of statins are elevation of hepatic enzymes, and myopathy. Elevated hepatic transaminases generally occur in 0.5% to 2.0% of patients and are a dose-dependent effect; progression to liver failure specifically due to statins is exceedingly rare. Myopathy induced by stain is also rare. Mild gastrointestinal symptoms (e.g., constipation, flatulence, dispepsia, and abdominal pain), are the most common adverse effects of lovastain. Thus, a lovastatin dose of 40 mg/day is well tolerated with low discontinuance rates (lower than 2%). [22]

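### Adherence, measured after randomisation, is a covariate in the efficacy model, so the lovastatin coefficient no longer estimates the intention-to-treat effect

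*Protocol article*

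**What the plan says.** The Analysis plan section opens with the principle: "The overall efficacy will be established with an intention-to-treat principle", with patients kept in their randomised group. Later in that section the time-averaged lovastatin versus placebo estimate "will be adjusted by the most important prognostic factors (baseline CD4+ T cell count, baseline viral load, and adherence to the treatment"), these being "considered as additional independent variables in the same GEE model". The reason given is that, even with randomisation, "this assignment process is not a guarantee against the possibility that estimates of treatment effect be modified by covariate imbalance".

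Two other sections show what adherence means here. Under Clinical follow-up, "The following clinical and pharmacotherapy parameters will be evaluated monthly for one year, during the medical control visits"; one of the listed items is "Adherence to therapy (lovastatin or placebo) and prevention of withdrawals". Under Interventions and safety of statins, each month's supply comes "from the pharmacist who also evaluates adherence to the intervention and gives usage recommendations". The only adherence measure taken before randomisation is the Morisky-Green test. It serves as an exclusion criterion and is not the covariate named in the model.

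**The concern.** Baseline CD4 count and baseline viral load are fixed before allocation. Adjusting for them is sound and usually gains precision. Adherence to the study drug is different: it develops after allocation and may respond to what was allocated. The protocol contains one such route, since study drug is stopped for serious adverse events or for set rises in transaminases or CPK, and it names hepatic and muscle effects as the main statin risks. An adherence gap between arms may therefore be a result of treatment and not a chance imbalance.

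With adherence in the model, the lovastatin coefficient compares patients at equal observed adherence. Randomisation does not protect that contrast. If good adherers also have a better or worse viral course for other reasons, part of that difference is credited to the drug or taken from it. The models affected are those for viral load (primary) and CD4 count (secondary).

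**Working it through.** **Mechanism.** Suppose lovastatin has no effect. Let *s* be the slope of the outcome on adherence within arms and *g* the adherence difference, lovastatin minus placebo. The coefficient adjusted for adherence is then 0 − *s* × *g*. It is zero only if *s* = 0 or *g* = 0. The documents give neither quantity, so both are assumed below.

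**Log-scale illustration (assumed values).** Adherence has an SD of 10 points and correlates 0.6 with an unmeasured factor acting after baseline, which lowers viral load by 0.10 log10 per SD.
- *s* = −0.10 × 0.6 = −0.06 log10 per SD of adherence.
- Lovastatin adherence 10 points lower (*g* = −1 SD): coefficient = −(−0.06)(−1) = −0.06; 10^−0.06 = 0.87, a false reduction of 13%.
- 5 points lower (*g* = −0.5 SD): −0.03; 10^−0.03 = 0.93, a false reduction of 7%.

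Simulation with 55 per arm and 2,000 runs gave −0.059 and −0.030 with adherence in the model, and 0.001 without it.

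**Simulation on the plan's own scale.** Inputs from Biostatistical considerations: SD 80,000 copies/mL, correlation 0.8, 55 per group, difference 22,500 copies/mL. There was one baseline and two follow-up measurements and 3,000 trials per scenario. The analysis was least squares on each patient's follow-up mean with robust standard errors, adjusted for baseline viral load. For complete data and covariates constant over time this equals exchangeable GEE. Adherence was one summary per patient, and baseline CD4 was not included.

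The setting agrees with the planned 80% power. The variance factor is (1 + 0.8)/2 − 0.8² = 0.26, so the SD is 80,000 × √0.26 = 40,792 and the SE is 40,792 × √(2/55) = 7,779. Then 22,500/7,779 = 2.89, which gives 82.4% power at two-sided 0.05.

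No true effect, adherence lower on lovastatin. Paired entries are for the two signs of the correlation between adherence and unmeasured prognosis:

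| Adherence gap (SD) | Correlation with prognosis | Estimate with adherence (copies/mL) | Type I error with adherence | Type I error without |
|---|---|---|---|---|
| 0 | 0.6 (one sign run) | +82 | 4.7% | 4.4% |
| 0.5 | 0 | +106 | 5.0% | 4.8% |
| 0.3 | 0.3 | −3,010 / +2,914 | 7.4% / 6.5% | 6.0% / 5.0% |
| 0.3 | 0.6 | −5,695 / +5,815 | 13.1% / 13.3% | 5.2% / 5.1% |
| 0.5 | 0.6 | −9,780 / +9,618 | 27.5% / 27.8% | 5.1% / 5.4% |
| 0.8 | 0.3 | −7,540 / +7,405 | 14.8% / 15.7% | 6.0% / 5.2% |
| 0.8 | 0.6 | −15,731 / +15,512 | 55.9% / 54.5% | 5.7% / 4.3% |

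As the formula requires, displacement is proportional to the gap. Dividing it by (gap × 80,000) gives about 0.24 in every row with correlation 0.6 and about 0.12 in every row with 0.3.

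With a true difference of −22,500, the model without adherence returns about −22,500 with 81% to 83% power in every scenario. With adherence, the estimate runs from −6,950 (power 17%) to −37,776 (power 99.9%), both at a gap of 0.8 SD and correlation 0.6.

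**The case against.** Four points can be made for the plan.

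- **The grouping is intact.** Patients are still analysed as randomised, so the literal definition of intention to treat is met. This stands. What is lost is the effect that the principle is meant to deliver.
- **An unadjusted estimate may also be reported.** The section first describes a coefficient for treatment alone with its Wald test, and brings in adjustment afterwards. That reading is possible, but the text does not name the unadjusted estimate as decisive, does not call the adjusted one secondary, and says the estimate will be adjusted in the same model.
- **The adherence gap may be small.** The trial is double-blind with identical pills, likely poor adherers are excluded, follow-up lipid results bypass the clinical investigators, and discontinuation at this dose is cited as below 2%. If 2% of lovastatin patients and no placebo patients took nothing, the gap would be 2 points, or 0.2 SD at the assumed SD of 10. The false effect would be 0.06 × 0.2 = 0.012 log10, about 3%. This is fair, although discontinuation does not capture missed doses.
- **Baseline viral load may absorb much of the bias.** If the unmeasured factor is a stable trait that also drives baseline viral load, the illustrative −0.06 and −0.03 log10 shrink to about −0.013 and −0.006 (about 3% and 1%). If it acts only after baseline, they do not shrink. The illustration is therefore the upper end of a range.

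The formula *s* × *g* also describes the case of no drug effect. With an active drug whose effect depends on intake, adherence carries part of that effect and the adjusted coefficient is harder still to interpret. None of these points is a reason to keep adherence in the efficacy model.

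**Conclusion.** The concern holds: the adjustment is wrong as written. It places a post-randomisation variable in the model that gives the primary and secondary efficacy results, and justifies it by an argument that applies only to variables fixed before allocation.

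That conclusion needs no assumption. The size does. Bias is nil if adherence is equal between arms or unrelated to prognosis. In the log-scale illustration, gaps of half to one SD give a false reduction of about 1% to 13%, depending on the gap and on whether the unmeasured factor also drives baseline viral load. The larger figures in copies/mL rest on gaps of 0.3 to 0.8 SD and correlations of 0.3 to 0.6, none of which comes from the documents. The direction cannot be known in advance, so the adjustment cannot be defended as conservative.

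**What to change.** Remove adherence from the GEE models for viral load and CD4 count, and keep baseline viral load and baseline CD4 count as covariates. State that this baseline-adjusted model is the decisive one. Report adherence by arm descriptively. Any analysis of its role should be labelled supplementary and use a method suited to post-randomisation variables.

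This is a one-line change to the protocol, and to the SAP if one exists. It needs no extra patients or data, and power stays at about 82% for the planned difference in the setting above. It should be made before the allocation sequence is disclosed for analysis.
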